### Outcomes

The primary perinatal outcome is a composite of perinatal death (as defined by in utero fetal death after randomisation or known neonatal death up to 7 days) or preterm delivery (less than 37 weeks’ gestation) or neonatal unit admission for at least 4 h (from infant delivery until hospital discharge). Each infant will only be counted once within this composite.

The secondary maternal outcomes are:Maternal serum concentration (between randomisation and delivery) of the following biochemical indices of disease: bile acids; alanine transaminase; aspartate transaminase; total bilirubin; gamma glutamyl transferaseItch between randomisation and delivery, measured by the worst episode of itch over the past 24 h (millimetres on a visual analogue scale, assessed at clinic visits)Gestational diabetes mellitusMode of onset of labourEstimated blood loss after delivery

The secondary short-term perinatal outcomes are:In utero fetal death after randomisationPreterm delivery (less than 37 weeks’ gestation)Known neonatal death up to 7 daysNeonatal unit admission for at least 4 h until infant hospital dischargeMode of delivery classified as spontaneous vaginal, instrumental vaginal or caesareanTotal number of nights in the neonatal unitBirth weightBirth- weight centileGestational age at deliveryPresence of meconiumAPGAR score at 5 minUmbilical arterial pH at birth

The following secondary outcomes will be described only and no formal statistical analysis comparing groups will be conducted:

#### Maternal

Maximum dose of trial medication requiredNeed for additional therapy for cholestasisAssessment of myometrial contractions by cardiotocography approximately 1 week (3–14 days) post randomisationReason for induction or pre-labour caesarean sectionMaternal death

#### Perinatal

Known neonatal death up to 28 daysNumber of nights in each category of care (intensive, high-dependency, special, transitional and normal)Need for supplementary oxygen prior to dischargeNumber of days when supplemental oxygen is requiredNeed for ventilation supportAbnormal cerebral ultrasound scanConfirmed sepsis (positive blood or cerebrospinal fluid cultures)Necrotising enterocolitis (Bell’s stages 2 and 3)Seizures (confirmed by electroencephalography or requiring anticonvulsant therapy)Encephalopathy (treated with hypothermia)Other indications and main diagnoses resulting in neonatal unit admission for at least 4 h

The following health resource use post enrolment will be captured for economic analysis:Maternal: total number of nights (antenatal, intrapartum and postnatal) together with level of care including adult Intensive Care Unit; mode of deliveryInfant: total number of nights for the infant in the neonatal unit, together with level of care (e.g. neonatal Intensive Care Unit)The cost of UDCA in the intervention group

All primary and secondary outcomes will be considered up to infant discharge home (from the hospital where delivered) or transfer to another hospital.

### Sample size

We will recruit 580 women in total; this will allow for the possibility of 5% of infants being lost to follow-up and is a conservative estimate given that some women will have twin pregnancies. The sample size is informed by the most recent Cochrane meta-analysis [13]. This includes the trials reported in the previous meta-analysis [14] with the addition of the largest trial published in 2012 by our group [2]. From these data, we estimate the event rate for the primary outcome (a composite of perinatal death or preterm delivery (less than 37 weeks’ gestation) or neonatal unit admission) for infants of untreated women as 40% with a plausible and relevant reduction to 27% for infants of women treated with UDCA, corresponding to an absolute risk reduction of 13% and a risk ratio (RR) of 0.675. This is conservative compared with the effect sizes seen in the Cochrane meta-analysis [13] for the three individual endpoints (RR 0.31, 0.46 and 0.48 for perinatal death, preterm delivery and neonatal unit admission, respectively). Five hundred and fifty infants of women with ICP (275 per group) are required to have a 90% chance of detecting, as significant at the two-sided 5% level, a reduction in the primary outcome measure from 40% in the control group to 27% in the treated group. Allowing for 5% lost to follow-up requires a total sample size of 580 infants (290 per group).

This number will also allow us to look at the components of the composite endpoints: a trial assessing 550 infants will have 89% power to demonstrate a reduction in neonatal unit admission rates from 17 to 8%, and 99% power for a reduction in prematurity from 41 to 23% (based on the Cochrane meta-analysis [13]), both effect sizes of the same magnitude as that demonstrated in our previous trial [2]. We do not anticipate enough perinatal deaths to detect reliably any plausible treatment effect, but we have included this due to its clinical importance and will report it separately.

The trial will be undertaken in approximately 30 consultant-led maternity units in England and Wales to achieve this sample size in the anticipated time-frame. Our previous pilot trial [2] has confirmed that women and clinicians are willing to participate in this randomised controlled trial and we have used recruitment estimates from this trial, together with trial management experience and expertise of the Co-investigator Group to inform strategies to meet the required target size.

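### The control rate for the composite is planned at 40% and for its own preterm component at 41%; the two cannot both hold and must be reconciled

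*Protocol article*

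**What the plan says.** All the planning figures are in the Sample size section of the protocol article.

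- **Source.** "The sample size is informed by the most recent Cochrane meta-analysis", together with the trials it contains.
- **Primary outcome.** It is described there as "a composite of perinatal death or preterm delivery (less than 37 weeks’ gestation) or neonatal unit admission". Its rate is estimated "for infants of untreated women as 40% with a plausible and relevant reduction to 27% for infants of women treated with UDCA". The section expresses this effect on two scales: 13 percentage points, and a risk ratio of 0.675.
- **Sample size.** 275 infants per group (550) for 90% power at the two-sided 5% level, and 580 after 5% loss.
- **Components.** The next paragraph states that "a trial assessing 550 infants will have 89% power to demonstrate a reduction in neonatal unit admission rates from 17 to 8" per cent, and "99% power for a reduction in prematurity from 41 to 23" per cent. Both are attributed to the same meta-analysis.
- **Pooled effects.** The section also quotes "RR 0.31, 0.46 and 0.48 for perinatal death, preterm delivery and neonatal unit admission, respectively" from that meta-analysis.

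The Outcomes section adds: "Each infant will only be counted once within this composite". The composite is therefore the union of its components.

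**The concern.** A union of events is at least as frequent as each event in it. A composite that includes preterm delivery cannot occur in 40% of control infants if preterm delivery alone occurs in 41% of them. The gap is one point on its face. It widens once admissions are counted, because any term infant who is admitted adds to the composite.

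The 40% is the base rate for the primary comparison. At 40%, a 13-point reduction and a risk ratio of 0.675 are the same effect. At any other base rate they differ, so the power of 550 infants then depends on which of the two is held. What is at stake is the written justification of the sample size, not the outcome definition or the analysis.

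**Working it through.** **Inputs** (all from Sample size): composite 40% vs 27%; preterm delivery 41% vs 23%; admission 17% vs 8%; 275 per group; two-sided 5%; 90% power; 5% loss. Allocation is 1:1 (Randomisation section).

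**Formulas** (pooled two-proportion test, no continuity correction; p̄ is the mean of the two rates):

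n per group = [1.960·√(2p̄(1−p̄)) + 1.2816·√(p₁(1−p₁) + p₂(1−p₂))]² / (p₁−p₂)²

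power = Φ{ [|p₁−p₂| − 1.960·√(2p̄(1−p̄)/n)] / √[(p₁(1−p₁) + p₂(1−p₂))/n] }

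**Step 1: reproduce the plan.**

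- 40% vs 27%: p̄ = 0.335; [1.960·√0.44555 + 1.2816·√0.4371]² / 0.0169 = 274.9, so 275 per group. Power at 275 is 90.0%.
- Loss: 275/0.95 = 289.5, so 290 per group and 580 in total.
- Admission, 17% vs 8% at 275 per group: 89.3% (stated 89%).
- Preterm delivery, 41% vs 23% at 275 per group: 99.6% (stated 99%).

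The stated arithmetic is right, so the problem lies in the inputs.

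**Step 2: bounds on the composite from the stated component rates, before deaths.**

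| | Lower bound (all admitted infants preterm) | Independence | Upper bound (no overlap) | Planned |
|---|---|---|---|---|
| Control | max(41, 17) = 41% | 1 − 0.59×0.83 = 51.0% | 41 + 17 = 58% | 40% |
| UDCA | max(23, 8) = 23% | 1 − 0.77×0.92 = 29.2% | 23 + 8 = 31% | 27% |

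The planned UDCA rate lies inside its bounds. The planned control rate lies below its lower bound.

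**Step 3: consequence if the 41% and 17% stand.** The two conventions are to hold the 13-point difference or to hold the risk ratio of 0.675.

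| Control composite | Power at 275, 13 points held | n per group for 90% | Power at 275, RR 0.675 held | n per group for 90% |
|---|---|---|---|---|
| 41% | 89.6% | 279 | 91.1% | 265 |
| 45% | 88.2% | 293 | 94.5% | 229 |
| 50% | 87.0% | 304 | 97.3% | 192 |
| 51% | 86.8% | 306 | 97.7% | 186 |
| 58% | 86.4% | 309 | 99.4% | 146 |

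For example, 41% vs 28% gives p̄ = 0.345; [0.13 − 1.960·√(0.45195/275)] / √(0.4435/275) = 1.259; Φ(1.259) = 89.6%.

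**Step 4: the preterm figures against the pooled risk ratio.** 23/41 = 0.56, against a quoted pooled value of 0.46; 41% × 0.46 = 18.9%. For admission, 8/17 = 0.47 against a quoted 0.48.

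**The case against.** The strongest reply is that the incoherence is one point wide and that much more can be read into it than the article supports. Four stronger readings are tempting, and each fails.

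- **That the 40% is the wrong figure.** The article shows only that 40% and 41% cannot both hold. Both are tied to the meta-analysis, but it cannot be seen whether they come from the same subset of trials. If the 41% is mistaken or does not apply to this population, the 40% may stand and the 41% to 58% range falls away.
- **That the trial misses 90% power at any coherent base rate.** This is true only if the 13-point difference is fixed. Even then the shortfall at 41% is 4 infants per group. If the risk ratio is held, which is the scale on which the Analysis section reports binary outcomes, power exceeds 90% throughout. With the component rates and independence in both groups (51% vs 29%), power at 275 per group is above 99.9%.
- **That the target effect is unclear.** As written it is clear: 40% to 27%, which is both 13 points and 0.675. The two part company only when the base rate moves.
- **That 0.46 and 41% to 23% contradict each other.** A pooled risk ratio is a weighted average over trials and need not equal the ratio of two crude rates. The article does not say that one was derived from the other.

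All four replies stand. They do not remove the central point. Rounding could close the gap between 40% and 41% only if almost every infant who was admitted or died was also preterm. The article calls its effect size conservative in comparison with the pooled risk ratios, but it does not say this of the base rate. Nor is this a detail left to a fuller document, since both rates are printed and they conflict.

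**Conclusion.** The point holds in a limited form. The planned control rates for the composite (40%) and for preterm delivery (41%) are jointly impossible for one population, so at least one planning figure is wrong as written. Which one cannot be settled from the article. The calculation of 275 per group is correct for the rates put into it.

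The size of the consequence is conditional. If the 41% and 17% stand, the control composite is 41% to 58% before deaths. Power at 275 per group then runs from 89.6% down to 86.4% with the 13-point difference held, or from 91.1% up to 99.4% with the risk ratio of 0.675 held. The largest loss is therefore under four points, and at the 41% minimum the change is negligible either way. These figures assume the pooled test, independent infants and the stated component rates. The gap between 0.46 and 0.56 merits a clarifying sentence and is not a demonstrated error.

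**What to change.** Reconcile the 40% composite rate with the 41% preterm rate in the Sample size section, and state which trials or data each came from.

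If the preterm rate stands, restate the control composite as at least 41%. Then give power for 275 per group across 41% to 58%, saying whether the 13-point difference (89.6% to 86.4%; 279 to 309 per group for 90%) or the risk ratio of 0.675 (91.1% to 99.4%) is held fixed. If instead the preterm rate is corrected, restate its component power. Add a sentence on how 41% to 23% relates to the pooled 0.46.

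This changes wording only. Recruitment stays at 580 and, according to the Trial status section, ended on 31 August 2018. The outcome and the analysis are untouched. The only cost is that the stated power may become slightly less favourable if the absolute difference is the target.

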### Randomisation

The allocation ratio of intervention (UDCA) to control (placebo) arms will be 1:1. Randomisation will be managed via a secure web-based randomisation facility. A minimisation algorithm will be used to ensure balance between the groups with respect to study centre (approximately 30 centres), gestational age at randomisation (< 34, 34 to < 37, ≥ 37 weeks’ gestation), single versus multi-fetal pregnancy, and highest serum bile-acid concentration prior to randomisation (< 40 μmol/L, ≥ 40 μmol/L).

The minimisation algorithm will be generated by MedSciNet, which will hold the allocation code. Research teams at sites will approach women to confirm eligibility and the intervention will be allocated using the web-based randomisation to provide an alpha numeric pack number which will correlate with a pack to be dispensed by that site’s pharmacy. The trial is triple-masked: trial participants, clinical care providers, outcome assessors and data analysts will all be masked to allocation.

Emergency code break will be available, but clinicians requesting unmasking must be satisfied that it is a genuine emergency and that knowledge of the treatment allocation (either UDCA or placebo) is needed to guide the appropriate clinical management of the participant. In some cases this may be achieved without unblinding, by stopping the allocated treatment and treating the participant with UDCA.

### Analysis

The analysis and presentation of results will follow the most up-to-date recommendations of the Consolidated Standards of Reporting Trials (CONSORT) group. Full details of the Statistical Analysis Plan are given in Additional file 1: Text S1. Analyses will be completed in Stata® version 13.1 or later. Unmasked data will only be made available for analysis after full database lock (after all data outcomes have been completed) or on request by the Data Monitoring Committee. All analyses will follow the intention-to-treat principle, i.e. all randomised women (and infants) will be analysed according to the treatment that they were allocated to, irrespective of the treatment they received or whether they received any treatment at all.

Demographic and clinical data will be summarised with counts and percentages for categorical variables, means with standard deviations for normally distributed continuous variables, and medians with interquartile or simple ranges for other continuous variables. All comparative analyses will be performed adjusting for minimisation factors at randomisation [15]. Centre will be included as a random effect. Both unadjusted and adjusted effect estimates will be presented, but the primary inference will be based on the adjusted estimates.

Binary outcomes will be analysed using log binomial regression models. Results will be presented as adjusted risk ratios plus confidence intervals. If any model does not converge, a Poisson regression model with robust variance estimation will be used [16]. Continuous outcomes will be analysed using linear regression models and results will be presented as adjusted differences in means with confidence intervals. Continuous outcomes will not be categorised for statistical testing unless pre-specified as an outcome (and clinically relevant). Unadjusted median differences with confidence intervals will be presented for skewed continuous variables, and an adjusted analysis using quantile regression will be presented if possible. Analysis of outcomes that are measured repeatedly over time (severity of itch and biochemistry measures) will use repeated measures analysis techniques. Alternatively, if the data are highly skewed, geometric means of the post-randomisation observations will be reported [17] and the trial arms will be compared using a geometric mean ratio, adjusted for the baseline measures and minimisation factors.

The analysis of perinatal outcomes will include all infants born to a randomised mother, so the denominator will be the number of infants. For these outcomes, correlations between twins will be accounted for in the adjusted model by nesting twin cluster as a random effect within centre. Multiplicity (multi-fetal pregnancy) will also be adjusted for as a fixed effect in the models.

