### Study procedures

#### Recruitment, eligibility and consent

Members of the research team will provide a full verbal explanation and written description of the trial to women who meet the inclusion criteria (as above). The woman will be given sufficient time to consider the information, and to decide whether she will participate in the trial. Written informed consent will be sought from the woman and taken by an appropriately trained physician. Baseline data, including all demography, serum bile-acid concentrations and liver function tests, together with an itch visual analogue score (worst itch in the previous 24 h) completed by the woman will be entered on a web-based database by members of the research team at the time of study enrolment. On completion of these details, the database will issue a pack number to the local hospital pharmacy for dispensing.

Participants will be reviewed at routine care clinic visits until delivery. Serum bile acids and liver function tests will be monitored according to usual clinical practice. The woman will be asked for a value of the worst itch she felt during the previous 24 h. The Investigational Medicinal Product (IMP) dose will be altered at the discretion of the responsible clinician. If maximal doses of the IMP have been reached, consideration can be given to the addition of other therapy, e.g. rifampicin, in addition to the trial therapy, without breaking the allocation code. The remainder of antenatal care, in particular the timing and mode of delivery will be left to the discretion of the responsible clinician. A schedule of participant enrolment, interventions and assessments in the trial is shown in Fig. 1.

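### The default repeated-measures analysis of itch and biochemistry names no baseline value of the outcome, although these values are recorded at enrolment and the skewed-data alternative uses them

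*Protocol article*

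**What the plan says.** The Analysis section of the protocol article gives a general rule: "All comparative analyses will be performed adjusting for minimisation factors at randomisation". Centre enters as a random effect, and the main inference rests on the adjusted estimates. The Randomisation section lists the other factors: gestation in three bands (below 34, 34 to below 37, and 37 weeks or more), single or multi-fetal pregnancy, and "highest serum bile-acid concentration prior to randomisation", split at 40 μmol/L. Itch is not among them.

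The section on recruitment, eligibility and consent shows what is available before treatment starts: "Baseline data, including all demography, serum bile-acid concentrations and liver function tests, together with an itch visual analogue score". The pack number is issued once these details have been entered.

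For itch and biochemistry, the Analysis section names repeated-measures techniques as the default and gives no covariates beyond the general rule. If the data are highly skewed, the arms are compared by a geometric mean ratio, "adjusted for the baseline measures and minimisation factors". The article refers to a separate SAP for full details.

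**The concern.** Two routes are described for the same outcomes. One names the baseline value of the outcome and the other does not. Whether baseline belongs in the model does not depend on skewness, so the difference has no evident reason.

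Read literally, the default route would adjust bile acid for a two-level version of its highest pre-randomisation value, and would adjust itch for nothing that measures itch. Baseline is usually the strongest predictor of a later value of the same measure. Leaving it out, or reducing it to two levels, widens the confidence interval without any saving. Bile acid and itch are also the outcomes that, with the primary outcome, are carried into the subgroup and adherence sensitivity analyses, so their precision is used more than once.

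**Working it through.** **The plan's own figure.** The Sample size section plans for the primary outcome with 90% power and a two-sided test at 5%. Its target is "a reduction in the primary outcome measure from 40% in the control group to 27% in the treated group". With pooled variance and no continuity correction:

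n per group = [1.960 × √(2 × 0.335 × 0.665) + 1.2816 × √(0.40 × 0.60 + 0.27 × 0.73)]² / 0.13² = (1.308 + 0.847)² / 0.0169 ≈ 275.

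That gives 550 in total. Dividing by 0.95 gives 290 per group, or 580. Both stated figures reproduce. They come from an unadjusted comparison of two proportions, so the choice of covariates changes neither.

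**Inputs for precision.** The article gives no baseline-to-follow-up correlation r and no share q of women at or above 40 μmol/L. Assumed values: r = 0.4 to 0.7, q = 0.35, and an approximately normal baseline (after log transformation if needed). For simplicity the two-level factor is treated as a split of the same baseline value. The plan's factor uses the highest earlier value, which need not be the enrolment value.

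**Bile acid: two levels against continuous.** A split keeps a fraction k of the correlation:

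k = φ(c) / √(q(1 − q)), with c the 65th percentile of the normal distribution = 0.385.

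k = 0.370 / 0.477 = 0.777, so k² = 0.603.

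SE ratio (continuous / two-level) = √[(1 − r²) / (1 − k²r²)]:

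- r = 0.4: √(0.840 / 0.904) = √0.930 = 0.964
- r = 0.6: √(0.640 / 0.783) = √0.817 = 0.904
- r = 0.7: √(0.510 / 0.704) = √0.724 = 0.851

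The SE falls by about 4% to 15%. In numbers of women, the variance ratios 0.930 and 0.724 mean that 7% to 28% fewer women would give the same precision. Put the other way, the two-level model would need 1/0.930 = 1.08 to 1/0.724 = 1.38 times as many, that is 8% to 38% more.

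**Sensitivity to the cut.** At r = 0.7, the two-level SE exceeds the continuous one by 16% if the cut falls at the median and by 19% if it falls at the 70th percentile. At r = 0.5 the figures are 6% and 7%, and at r = 0.3 about 2%. The correlation matters far more than the place of the cut.

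**Itch: baseline absent against included.** SE ratio = √(1 − r²):

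- r = 0.4: √0.84 = 0.917
- r = 0.7: √0.51 = 0.714

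The SE falls by about 8% to 29%. This applies only if baseline itch is wholly absent from the default model.

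**Other outcomes.** In 400 simulated trials of 550, with an assumed link between gestation and outcome and three assumed gestation distributions, adding continuous gestation cut the SE by about 3% for gestational age at delivery. For the primary log risk ratio the cut was 0.5% to 1%.

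**The case against.** The strongest reply is that this rests on silence. The article condenses a fuller plan and refers to an SAP that is not shown. The form of covariates is ordinary SAP content, and repeated-measures techniques can take baseline as a covariate or as part of the response. The one place where the article spells out a model for these outcomes does include baseline, which suggests that the authors intended it throughout.

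Much of this stands. A reader might infer that every model uses only the coarse categories, or that baseline itch is certainly ignored. The documents support neither reading: the geometric-mean route includes baseline, and the article does not say in what form the minimisation factors enter any model. A reader might also infer a material loss for the primary outcome. The gain there is about 1% or less, and extra terms could make convergence harder in log-binomial models that already carry centre and twin random effects.

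What survives is narrower. The article states a rule for all comparative analyses and then attaches a baseline term to only one of two routes for the same outcomes. An analyst following the default route as written would not be told to include it.

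**Conclusion.** A minor point of efficiency and wording. Adjusting for the minimisation factors is valid; there is no bias, no effect on the type I error rate and no change to 550 or 580. As written, the default route for itch and biochemistry leaves out a baseline value that the trial collects.

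If that route were followed literally, the SE would be larger than it need be. Including the continuous baseline would reduce it by about 4% to 15% for bile acid and 8% to 29% for itch. These ranges rest on an assumed correlation of 0.4 to 0.7, and the bile-acid range also on an assumed 35% of women at or above 40 μmol/L. Neither figure is in the article. If the SAP already includes baseline, the loss does not arise and only the article's wording needs attention.

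**What to change.** Keep the minimisation factors and centre in all models. State that the repeated-measures models for itch and for each biochemical index also include the continuous enrolment value of that outcome, on the log scale where skewed, as the geometric-mean route already does. If the SAP says this already, one clarifying clause is enough.

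Optionally, add continuous gestation at randomisation to the linear model for gestational age at delivery, for a gain of about 3% in SE under the simulated assumptions.

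Leave the log-binomial models for the primary and other binary outcomes unchanged. The cost is a sentence of analysis text, settled before unmasked data are seen. No new data are needed. The repeated-measures and linear models do not share the log-binomial convergence problem, for which a Poisson fallback is in any case already specified.

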The main clinical research question is whether adverse pregnancy outcomes can be reduced in women with ICP by treatment with UDCA. This is a subject of intense debate. The current UK guideline (from the Royal College of Obstetricians and Gynaecologists) on the management of ICP describes the evidence relating to the use of UDCA and states that ‘UDCA improves pruritus and liver function in women with obstetric cholestasis’ but ‘women should be informed of the lack of robust data concerning protection against stillbirth and safety to the fetus or neonate’. The guideline concludes that: ‘as the pathophysiology of obstetric cholestasis and the mechanism of fetal demise are uncertain, the possible role of UDCA is unclear. Further larger studies are required to determine this’. The latest updated Cochrane review [13] judged many of the trials of UDCA in ICP to be at moderate to high risk of bias. Trials to date have lacked power to demonstrate whether UDCA is fetoprotective, with numbers of participants and adverse events too small to enable the recommendation of UDCA. The Cochrane review concluded that larger trials of UDCA to determine fetal benefits or risks are needed.

If UDCA is found to be beneficial in ameliorating adverse perinatal outcomes, once published these results would be highly likely to lead to an immediate change in clinical practice, through individual choice of clinicians and women, and through changing national/international guidelines.

The PITCHES trial is a triple-masked, placebo-controlled randomised trial to evaluate UDCA versus placebo in women with ICP between 20^+ 0^ to 40^+ 6^ weeks’ gestation. The primary objective of the trial is to determine if UDCA treatment of women with ICP between 20^+ 0^ and 40^+ 6^ weeks’ gestation reduces adverse perinatal outcomes up to infant hospital discharge. The secondary objectives of the trial are (1) to investigate the effect of UDCA on other short-term outcomes for both mother and infant and (2) to assess the impact of UDCA on health care resource use, in terms of the total number of nights for mother and infant, together with level of care.

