### Economic analysis

Data on mother and infant inpatient care and mode of delivery will be costed using nationally published sources. The cost of UDCA (derived from *British National Formulary*, National Institute for Health and Care Excellence) will also be included for women randomised to receive the intervention. Descriptive statistics will be reported including mean cost per participant and 95% confidence intervals constructed using bootstrapping.

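### The rule for skewed outcomes gives 0 versus 0 for total neonatal unit nights on the plan's own admission rates, so it says nothing about the infant-nights part of secondary objective 2

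*Protocol article*

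**What the plan says.** All references are to the protocol article.

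- **Objective.** The second secondary objective (Background) is "to assess the impact of UDCA on health care resource use, in terms of the total number of nights for mother and infant". It also takes in the level of care.
- **Outcome.** The Outcomes section lists total nights in the neonatal unit among the secondary perinatal outcomes. It stands ahead of the separate list that will only be described, so it is formally compared.
- **Denominator.** The Analysis section says: "The analysis of perinatal outcomes will include all infants born to a randomised mother, so the denominator will be the number of infants". An infant who is never admitted therefore counts as zero nights.
- **Rule for continuous outcomes.** "Continuous outcomes will be analysed using linear regression models and results will be presented as adjusted differences in means with confidence intervals".
- **Rule for skewed outcomes.** "Unadjusted median differences with confidence intervals will be presented for skewed continuous variables". The adjusted counterpart is conditional on feasibility: "an adjusted analysis using quantile regression will be presented if possible". No quantile level is given, and neither rule names the outcomes it covers.
- **Planned admission rates.** The Sample size section states that "a trial assessing 550 infants will have 89% power to demonstrate a reduction in neonatal unit admission rates from 17 to 8" per cent.
- **Costs.** The Economic analysis section reports mean cost per participant with "95% confidence intervals constructed using bootstrapping".

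**The concern.** Nights in the neonatal unit, counted over all infants, has a large block of zeros and a long right tail. Skewness is the only trigger for the median rule, so the natural reading of the Analysis section sends this outcome there. If far fewer than half of the infants are admitted, the median is zero in both arms and cannot move. The trial could then report zero nights in each arm and a difference of zero even if UDCA halved neonatal bed use, and a reader could take that for evidence of no effect. The same section rests inference on adjusted estimates. For a skewed outcome, however, the adjusted analysis is conditional on feasibility, and the part that is certain to be reported is the unadjusted zero.

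**Working it through.** **Inputs.** Admission 17% (control) and 8% (UDCA), 275 infants per group, and composite rates of 40% and 27%, all from Sample size. All infants form the denominator (Analysis).

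**1. Reproduce the plan's figure.** Power for 17% versus 8%, two-sided 5%, pooled variance under the null, no continuity correction:

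- mean rate = (0.17 + 0.08)/2 = 0.125
- SE under the null = √(2 × 0.125 × 0.875/275) = 0.0282
- SE under the alternative = √((0.17 × 0.83 + 0.08 × 0.92)/275) = 0.0279
- z = (0.09 − 1.96 × 0.0282)/0.0279 = 1.24, so power = 89.3%, against 89% stated.

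The admission rates are thus the ones the plan itself works with.

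**2. Share of zeros.** 1 − 0.17 = 83% in controls and 1 − 0.08 = 92% with UDCA. Both exceed 50%, so both medians are 0 and their difference is 0.

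**3. Could a sample median be non-zero by chance?** With 275 infants, at least 138 would need one or more nights. The binomial tail P(X ≥ 138) is:

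| Admission rate | Basis | P(sample median > 0) |
|---|---|---|
| 8% | planned, UDCA | 1.5 × 10⁻⁷⁵ |
| 17% | planned, control | 1.9 × 10⁻³⁶ |
| 27% | every UDCA composite event an admission | 2.9 × 10⁻¹⁶ |
| 40% | every control composite event an admission | 4.0 × 10⁻⁴ |

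Admission for at least 4 h is a component of the composite, so the last two rows are the ceiling that the plan's own rates allow.

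**4. Another definition of the median difference.** The Hodges–Lehmann estimate is the median of all between-arm pairwise differences. On the planned rates 0.83 × 0.92 = 76% of pairs are zero against zero, so it is 0 as well. At the 40%/27% ceiling the control infant has the longer stay in at most 40% of pairs and the UDCA infant in at most 27%. Neither reaches half, so the estimate is still 0.

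**5. Quantile regression.** At the median it meets the same block of zeros: the conditional median is 0 in any covariate stratum where fewer than half of the infants are admitted. The article gives no stratum-specific rates. Only quantiles above about the 83rd percentile (control) and the 92nd (UDCA) are non-zero, and these describe the tail rather than total nights.

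**6. Illustration of what is lost.** The article gives no length of stay. *Assumed* log-normal stays in admitted infants, 275 per group, 17% versus 8% admitted, 2,000 simulated trials per row:

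| Assumed median stay (log-SD) | Median difference equal to 0 | Average mean difference, nights per infant | Welch t-test power | Rank-test power |
|---|---|---|---|---|
| 3 nights (0.8) | 100% of trials | −0.42 | 68% | 90% |
| 5 nights (1.0) | 100% of trials | −0.80 | 58% | 90% |
| 8 nights (1.0) | 100% of trials | −1.22 | 56% | 90% |

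In one data set from the middle scenario the bootstrap 95% interval was [0, 0] for the median difference and [−2.05, −0.30] for the mean difference. Steps 2 to 4 do not depend on these assumed stays.

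**The case against.** **The rule does not name this outcome.** True. A difference in means is also in the plan, and a quantile other than the median is not excluded. But skewness is the stated trigger and this outcome plainly meets it. Using the mean would depart from the rule as written, and picking the branch or the quantile after seeing the data is what pre-specification is meant to prevent.

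**The analysis plan in Additional file 1 may settle it.** It may, and it is not shown. The point is not that detail is absent: a rule stated in the article fails on the article's own figures for a listed outcome. If the full plan differs, the two texts need reconciling.

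**A reader might infer that secondary objective 2 cannot be answered at all.** The documents do not support that. The objective also covers maternal nights and level of care, and no figure suggests that maternal nights have a zero median. Nights in each category of neonatal care are to be described. The Economic analysis carries mother and infant inpatient care into mean costs with bootstrap intervals, which are not degenerate. That analysis is descriptive, however, and in cost rather than nights, so it does not replace a between-arm estimate for infant nights.

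**A fall in neonatal unit use would show elsewhere.** In part. Admission is itself compared, with 89% stated power, so an effect through admissions should be seen. An effect on length of stay, or the size of the effect in nights, would not.

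**Unadjusted fallback.** The article does say that inference rests on adjusted estimates, and the feasibility caveat is not in itself a contradiction. It adds little to the main point.

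**Conclusion.** The point holds for one outcome. If the rule for skewed variables is applied to neonatal unit nights over all infants, as its wording most naturally requires, both medians and their difference are 0 whatever UDCA does, provided fewer than half of the infants in each arm are admitted. The planned rates (17% and 8%) are far below that limit, and so is the composite ceiling (40% and 27%). The result rests on those rates and on non-admitted infants counting as zero; it needs no assumption about length of stay. The mean differences and powers in the simulation do need one and are only illustrative.

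The consequence is confined to the infant-nights part of secondary objective 2. The primary outcome, the sample size, maternal nights, level of care and the mean-cost analysis are untouched. This is a moderate issue that deserves correction but does not threaten the trial's main conclusion.

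**What to change.** For total neonatal unit nights, replace the median rule in the Analysis section, and any matching text in the full analysis plan, with:

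- **Estimate.** An adjusted difference or ratio of mean nights per infant, zeros included, adjusted for the minimisation factors. Choose one scale in advance; a log-link count-type model would give the ratio.
- **Interval.** Bootstrap or robust, clustered on the mother to allow for twins.
- **Denominator.** All infants born to a randomised mother, as the Analysis section already sets out, with an explicit statement of how fetal deaths and neonatal deaths enter the count.
- **Description.** Median and interquartile range among admitted infants only, labelled as descriptive because admission may itself be affected by treatment.

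No new data are needed, and bootstrap intervals are already planned for costs. The downside is statistical: a mean is less robust than a median, and a few long stays will weigh heavily and widen the interval. Presenting the result next to the admission comparison would help readers see whether a difference comes from fewer admissions or from shorter stays.
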